## Abstract

**Background:**

Use of community volunteers to support vulnerable families is a widely employed strategy with a long history. However, there has been minimal formal scientific investigation into the effectiveness of volunteer home visiting programs for families. There is also a need for research examining whether volunteer home visiting leads to improved outcomes for volunteers.

**Objective:**

The objective of this paper is to describe the research protocol for a pragmatic randomized controlled trial (RCT) of the Volunteer Family Connect intervention, a volunteer home visiting program designed to support families of young children who experience social isolation or a lack of parenting confidence and skills. The project is being conducted in partnership with 3 leading not-for-profit organizations, designed to contribute to the body of evidence that informs decisions about appropriate family support services according to the level of need. It is the first study to examine outcomes for both the families and the volunteers who deliver the service.

**Methods:**

The RCT is being conducted in 7 sites across Australia. We aim to recruit 300 families to the study: 150 control (services as usual) and 150 intervention (services as usual + volunteer home visiting) families. Intervention families will receive the service for 3-12 months according to their needs, and all participants will complete 6 data collection points over 15 months. A minimum of 80 volunteers will also be recruited, along with a matched community comparison group. The volunteers will complete 3 data collection points over 12 months. Primary outcomes include community connectedness and parenting competence. Secondary outcomes include parent physical and mental health; general parent well-being; parent empowerment; the child-parent relationship; sustainability of family routines; child immunization; child nutrition or breastfeeding; number of accidental injury reports; and volunteer health, well-being, and community connectedness.

**Results:**

This effectiveness trial was funded in 2016, and we aim to complete data collection by the end of 2018. The first results are expected to be submitted early in 2019.

**Conclusions:**

There is a need to rigorously assess volunteer home visiting and whether it has a unique and important role on the service landscape, complementary to professional services. This research is the first trial of a volunteer home visiting program to be conducted in Australia and one of the largest of its kind worldwide.

**Trial Registration:**

Australian New Zealand Clinical Trial Registry ACTRN12616000396426; https://www.anzctr.org.au/Trial/Registration/TrialReview.aspx?id=370304 (Archived by WebCite athttp://www.webcitation.org/70q42fU7V)

**Registered Report Identifier:**

RR1-10.2196/1000

## Introduction

Volunteer home visiting is a widely adopted community-based approach to support families, linking vulnerable and isolated families to trained volunteers from their local communities who have experience in parenting or caring for children. Volunteer home visiting programs can take different forms, with many seeking to support families by helping them strengthen their social and community networks, providing families with connections to appropriate local health, welfare, and education services and support information [1]. Volunteers may also work with parents to increase their parenting confidence, encourage positive parent-child relationships, share local knowledge, and foster a sense of belonging and community resilience [2]. Bronfenbrenner’s bioecological model [3,4] emphasizes that building resilience in both parents and the communities in which they live is critical to achieving family physical, mental, and social well-being. Bronfenbrenner described a complex and dynamic web of relationships that exist between children, their families, the settings in which children participate, and the wider community. Child health and well-being outcomes are strongly influenced by the many social and environmental contexts that operate within a child’s life. Factors across contextual layers accumulate to increase a child’s or a parent’s resilience or risk factors. This requires the development of social infrastructure to support the growth of inclusion networks and opportunities for meaningful civic participation [1].

While previous research has demonstrated that a sense of belonging and inclusion in the local community context is fundamental to health and well-being [5,6], there are increasing reports of isolation, segregation, and nonparticipation in response to changing community environments [7]. A sense of isolation is particularly evident in research examining the social inclusion of families in need of additional supports, such as new arrivals to a country [8], those with demanding care responsibilities [9,10], and those who experience cognitive limitations or mental health challenges [11].

There is an argument for volunteer home visiting having a unique and necessary place on the landscape of services available to families because of the following reasons: (1) It fills the service gap for families whose circumstances do not meet the eligibility criteria for targeted or sustained professional home visiting services and yet need more support than is available from universal primary health and community services and (2) It is designed to break down potential barriers to service access, such as language, transport, or cultural barriers. Another unique feature of the volunteer home visiting model is that there are two groups within the community who, according to emerging evidence, potentially benefit—the families who receive the service and the volunteers who deliver the service [12-14].

Despite its long history and critical role within Australian service systems, there has been relatively little formal scientific investigation into the effectiveness of volunteer home visiting programs. Comprehensive reviews criticize the available evidence for volunteer home visiting as being largely characterized by research with methodological limitations that is focused on program satisfaction and experiences of participation rather than outcomes [15,1]. Nonetheless, findings from the existing literature suggest there is a role for volunteer home visiting in supporting families with vulnerabilities. International research indicates that this service model may provide an acceptable vehicle for the distribution of health and parenting information [16] and improve family social support networks, both in terms of social capital as well as family social connectedness [17,18]. It has also been shown that volunteer support can contribute to improved outcomes relating to parental emotional well-being [19,20], parental sense of competence [21-23], parent-child relationships [24], and parenting behaviors and skills [25]. There is particularly strong evidence that peer support can play a key role in promoting increased rates of breastfeeding and child immunization [26-28]. There is also potential for volunteer home visiting models to play an important support role in the care plans of those with chronic health conditions [29]. It should be noted, however, that community volunteers may not have a marked impact on clinical outcomes, which may be more appropriately addressed by professional services [30], and volunteer support needs to be provided within the context of well-developed guidance and supervision [31,32]. The small number of studies that examine volunteering in the context of family support programs suggest that volunteers experience positive outcomes such as increased knowledge and skills, a stronger sense of social cohesion, reduced loneliness and isolation, and an improved sense of purpose and confidence [11].

The aim of this research is to rigorously explore the effectiveness of the Volunteer Family Connect program (ACTRN12616000396426), a volunteering home visiting program collaboratively designed by a consortium of researchers and service providers in Australia to support families of young children who are vulnerable because they experience social isolation or a lack of parenting confidence and skills. Volunteer Family Connect is a community-based strategy that aims to improve the well-being, social connection, and parenting of vulnerable families with young children and the well-being and social connection of community members who volunteer. The results can be used to inform public policy on this issue.

## Methods

### Study Design

A pragmatic randomized trial design is being undertaken to provide high-quality evidence to assess the impact of the Volunteer Family Connect program. Pragmatic trials are a rigorous method for assessing effectiveness, that is, the degree of beneficial effect of intervention programs in real-world conditions, answering the question “Does this intervention work under usual conditions?” [30]. In keeping with the “real-world” conditions for a pragmatic randomized trial, in this study, we performed the following:

We recruited the full range of families referred to the volunteer home visiting programs of the partner organizations through usual referral processes, with no changes to service inclusion and exclusion criteria.We compared the volunteer home visiting program with other usual care support services, such as group activities and referral to other agencies.We tested real-world implementation of the volunteer home visiting program by our service partners with their current volunteer providers using guidelines to support quality service provision, but acknowledging that there are variations in practice, while rigorously assessing outcomes using standardized measurement tools.

The design of the study was supported using the PRagmatic Explanatory Continuum Indicator Summary (PRECIS) tool [33], which assesses the varying degrees of pragmatic (effectiveness) and explanatory (efficacy) trial approaches. Wider webs represent more pragmatic trials: narrow webs represent more explanatory trials. The PRECIS web for the current trial is depicted in Figure 1. Rating of the Volunteer Family Connect trial on the PRECIS tool was completed collaboratively by the research team. All senior members of the research team gathered in a face-to-face meeting and discussed the project as it is reflected in scores on the PRECIS tool until consensus was achieved.

### Primary Research Question

Is a volunteer home visiting service intervention effective in improving the parenting competence and community connectedness of vulnerable families with young children compared with families who receive usual care services in the community?

**Figure 1 figure1:**
[figure not shown]
Using the PRagmatic Explanatory Continuum Indicator Summary tool to describe the Volunteer Family Connect randomized controlled trial.

### Hypothesis

Families receiving a volunteer home visiting service intervention will have significantly better family outcomes at 15 months post program entry (higher sense of parenting competence and stronger community support networks) than those allocated to continue to receive usual community-based support services.

### Secondary Research Questions

Do differences exist in the patterns of parent health, well-being, and empowerment and the sustainability of family routines over time between those who receive the Volunteer Family Connect program and those in the services as usual control group?Does volunteer home visiting lead to differing outcomes for children aged 0-5 years in intervention families compared with those in control group families on measures of immunization, breastfeeding duration, nutrition, and accidental injury?Do different patterns of outcomes for intervention families depend on the location (ie, availability and accessibility of health, welfare, and early childhood services in the local area) and the duration of the program (ranging from 3 to 12 months)?Does volunteering on the Volunteer Family Connect program lead to differing outcomes on measures of well-being, health, community connectedness, and self-efficacy for volunteers over time compared with a matched community comparison group?

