### Intervention

#### Development

The Volunteer Family Connect program was developed in conjunction with 3 leading not-for-profit organizations, all involved in coordinating volunteer home visiting programs in the eastern states of Australia: The Benevolent Society; Good Beginnings Australia (later subsumed into Save the Children Australia); and Karitane. An executive member from each partner organization along with the research leaders met every 6 weeks for approximately 5 years. Collaboratively, a “best practice” model of volunteer home visiting was developed based on a shared theory of change, the strengths of the existing programs, practice wisdom, and existing research evidence. The program was manualized, and practice tools were created such as fidelity checklists, family progress tools, and volunteer training schedules. The Volunteer Family Connect program is currently being implemented with fidelity in 7 trial sites across 4 states (New South Wales, Queensland, Tasmania, and Victoria) including city, suburban, and rural settings.

Preparation for the trial has also involved extensive and ongoing consultation and support for program coordinators and provision of training across all levels of the partner organizations (including volunteers) to increase the understanding of, and support for, the conduct of an RCT.

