
#### Control Group, Services as Usual

Neither intervention nor control group families are limited in the extent to which they are able to access other services within the community. It is anticipated that most families will access a range of early childhood health and education services. Family use of other services will be documented in the research, based on parent self-report, and explored as a variable in analysis.

**Table 1 table1:** Outcome measures.

Outcomes and Construct Measured			Data Collection Schedule						Instrument
			Enrollment (Baseline)	Months					
				3	6	9	12	15	

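### The location question is posed for intervention families alone, so an answer as worded cannot separate ordinary area differences from differences in program effect

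*Protocol article*

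**What the plan says.** The third item under Secondary Research Questions asks: "Do different patterns of outcomes for intervention families depend on the location". It explains location as "availability and accessibility of health, welfare, and early childhood services in the local area", and the same sentence adds program duration as a second factor.

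The neighbouring family questions are framed differently. The parent question looks for differences "between those who receive the Volunteer Family Connect program and those in the services as usual control group". The child question asks about outcomes "in intervention families compared with those in control group families on measures of immunization" and other child measures. The volunteer question also has a comparator, a matched community group. Only the location and duration question has none.

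The other relevant facts are these:
- The Development section describes "7 trial sites across 4 states (New South Wales, Queensland, Tasmania, and Victoria) including city, suburban, and rural settings".
- On usual care, the article states: "Neither intervention nor control group families are limited in the extent to which they are able to access other services within the community".
- Allocation is by individual family, nominally 1:1, and becomes proportional when families outnumber available volunteers.
- The Outcomes section says that measures are the same in both family groups, apart from satisfaction with the program.
- Quantitative Analysis names a mixed model for the intervention effect over time, adjusted for confounders. It mentions no location term.

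**The concern.** Connectedness, parenting competence and natural improvement may differ between a city, a suburban and a rural area with or without a volunteer. Location is defined here by local services, and those services are open to both arms. The location factor can therefore move outcomes in families who never meet a volunteer.

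If only intervention families are compared, an area where all families do well looks the same as an area where the program does well. The conclusion could even be reversed: a well-served area might show the best intervention-arm outcomes although the volunteer adds least there. The article presents the program as filling a gap between universal and intensive services and wants its results to inform public policy. Where the program adds most is therefore a question that readers will take from this objective.

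**Working it through.** **What each comparison estimates.** Let the mean outcome at location *j* be a_j for controls and a_j + d_j for intervention families, where a_j is the area level and d_j the program effect there.
- Locations *j* and *k*, intervention families only: (a_j − a_k) + (d_j − d_k).
- Intervention-control difference at *j* minus that at *k*: d_j − d_k.

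Only the second isolates a difference in program effect. Covariate adjustment within the intervention arm does not supply the missing controls.

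**Inputs from the article.** 7 sites; 150 families recruited and 100 analysed per arm; two-sided alpha 0.05. **Assumptions.** Equal site sizes; the same program effect at every site; site ICC from 0 to 0.10; one outcome time point without baseline adjustment. The 7-site test is an illustration, because the article specifies no test for this question.

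**The plan's own figure.** None is given for location. For the main comparison, Sample Size states power .80 at an effect size of .5 with 100 per group. The normal approximation gives Φ(0.5/√(2/100) − 1.96) = 0.94, so .80 is a conservative floor. It has no bearing on this point.

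**Site test within the intervention arm.** With *n* families per site, the F statistic is inflated by L = 1 + n·ICC/(1 − ICC). The rejection rate is P(F > c/L), where c is the 5% critical value. For 100 families, n ≈ 14 and c = 2.20 on 6 and 91 degrees of freedom. For 150, n ≈ 21 and c = 2.16 on 6 and 140. The simulation used 3,000 trials per setting.

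| ICC | L (n=14) | Formula, 100 | Simulated, 100 | Formula, 150 | Simulated, 150 |
|---|---|---|---|---|---|
| 0 | 1.00 | 5% | 5.1% | 5% | 5.0% |
| 0.01 | 1.14 | 8.5% | 9.0% | 11% | 11.0% |
| 0.02 | 1.29 | 13% | 12.6% | 18% | 16.3% |
| 0.05 | 1.74 | 28% | 28.2% | 41% | 41.7% |
| 0.10 | 2.56 | 53% | 54.5% | 69% | 69.8% |

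In the same simulations the site-by-arm interaction test rejected in 4.3% to 5.2% of trials.

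**Size in outcome units.** The true means of two sites with the same program effect differ with SD √(2·ICC), in units of the total outcome SD. This is 0.14 at ICC 0.01 and 0.45 at ICC 0.10. The plan treats an effect size of about 0.5 as clinically meaningful.

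**Price of the interaction.** Split the sites into two location types, with half of each arm in each. The standard error of the interaction is √(4/n), where n is families per arm and type.
- 100 per arm: √(4/50) = 0.283. The detectable interaction at 80% power is 0.283 × 2.80 = 0.79 SD. Power for 0.5 SD is Φ(0.5/0.283 − 1.96) = 42%.
- 150 per arm: √(4/75) = 0.231. The detectable interaction is 0.65 SD, and power for 0.5 SD is 58%.

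**Are there controls at each site?** With 200 analysed families, a site has about 28. The chance that all 28 are intervention families is 0.5^28 ≈ 4 × 10⁻⁹ at 1:1. If the article's 5:2 example applied throughout, it is (5/7)^28 ≈ 8 × 10⁻⁵.

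**The case against.** The strongest reply is that the article poses a question and fixes no analysis for it. It names no site-by-site test and nowhere restricts an analysis to the intervention arm. The one longitudinal method it names for family outcomes is a mixed model of the intervention effect, which uses both arms. An analysis plan that is not shown may add a location-by-arm term. Asking how outcomes of program families vary by place is also a common informal way of asking where a program works. In addition, use of other services is to be documented and explored in analysis, apparently in both arms.

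Much of this stands. A reader might infer that the trial will report area differences as program success; the article does not say so. A reader might also take controls at every site as stated. They are very likely under individual randomization, but the article mentions no stratification by site and lets the allocation ratio follow volunteer supply. Nor are the rejection rates error rates for the literal question: if areas differ, outcomes do depend on location. They become false findings only when read as differences in program effect. The ICC is assumed, and at ICC 0 there is no excess. Baseline adjustment could remove stable area differences, though not area differences in natural change over time.

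What does not stand is that this is only detail left for later. The article itself fixes whom the question is about, departs from its neighbouring questions in doing so, and nowhere brings controls back in. An analysis that follows the wording inherits the problem.

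**Conclusion.** The point holds as a badly worded secondary question, not as a prediction of misreporting. Answered as written, a location difference mixes area and program effect and could be misread as the program working better in some places.

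Under the stated assumptions (equal sites, identical program effect, ICC 0.01 to 0.10, no baseline adjustment, about 100 intervention families), roughly 9% to 53% of trials would show a significant location difference, against about 5% for the interaction test. The range follows almost entirely from the assumed ICC and may be too high once baseline is adjusted for.

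The primary question, the hypothesis, the parent and child questions and the overall effectiveness rule are untouched. The change is worth making because it needs no new data.

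**What to change.** Reword the location part to: *Does the difference between intervention and control families depend on location?* Answer it with a location-by-arm term in a model that uses both arms and includes location main effects and baseline adjustment. Report the arm difference with its confidence interval by location, and do not present a comparison among intervention families alone as a program finding. Label the result exploratory, and any link with local service availability descriptive, because power is low and there are only 7 sites. Confirm that each site contributes controls.

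Treat duration as a separate question. Controls have no program duration, so the same rewording does not repair it.

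The cost is one sentence and one model term. The estimates will be less precise than within-arm contrasts: for the two-way split at 100 per arm, the detectable difference rises from 0.56 SD to 0.79 SD. An inconclusive answer is therefore more likely.

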### Participants

#### Eligibility Criteria

Eligible families will be those who meet the following criteria: (1) families having one or more children in the 0-5 age range; (2) families at risk of geographic or social isolation (eg, separated from usual support networks due to immigration); (3) parents seeking to develop confidence and increase their parenting knowledge and skills; (4) families residing in the specified service area; and (5) families unable to resource or access other support services (eg, due to financial hardship). Language translation services have been secured so that families with a first language other than English will not be excluded from participating in the research.

Families will be ineligible for the study if any of the following conditions apply: (1) there is active abuse or domestic violence within the family; (2) there is unmanaged mental illness within the family; (3) substance abuse is an issue within the family; (4) the family is living in an environment unsafe for the volunteer to visit; and (5) the family is under child protection orders or there are unsettled parenting arrangements. Families referred for volunteer home visiting will be assessed for eligibility by the local Volunteer Family Connect program coordinator according to the usual practice, and referrals will be made to other services within the community if the family is ineligible.

All current volunteers within the Volunteer Family Connect program will be invited to participate in the study. It is not possible to examine outcomes for volunteers employing a randomized controlled trial (RCT) design because this would halve the number of volunteers available and significantly impact program implementation. Instead, a community comparison sample will be recruited that will be matched on age, gender, education and employment levels, and geographical location.

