#### Recruitment

Family participants will largely be identified through the Volunteer Family Connect usual service referral networks, which include child and family health nurses, general practitioners, or family support workers. The Volunteer Family Connect program is advertised within the community, and parents are welcome to self-refer to the program. If eligible for the program, families will be invited to speak to a member of the research team and, if interested, informed consent for the research will be secured. The family will then be randomly allocated by the research manager using computer-generated random numbers to receive either the volunteer home visiting program in addition to usual care services (Intervention group = Volunteer Family Connect + usual care services) or the usual care services only (Control group = usual care services).

The procedure used to recruit and allocate families is summarized in Figure 2.

An invitation will be extended to all volunteers currently involved with the 7 participating sites to participate in the research. The matched community comparison sample will be recruited via one of the following two strategies: (1) volunteers will be asked to pass on an invitation to participate in the research to nonvolunteering acquaintances in their local networks and (2) the research will be advertised through Facebook, targeting the local areas in which the Volunteer Family Connect program is being trialed.

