**Figure 2 figure2:**
[figure not shown]
Participant flow diagram.

The families will participate in data collection for a period of 15 months. Strategies have been put in place to support and encourage the retention of participants, including asking all participating parents to provide the name and phone number of a relative or friend who can be contacted by the researchers if we struggle to reach them; providing families with the contact details of the research team and asking them to advise us if their contact details change; providing each family with an Aus $20 gift voucher for a popular grocery store chain at each data collection point and sending thank you notes; and employing project offices who have strengths in the building of rapport with families. The decision to employ these strategies was primarily based on the positive experiences of the research team in the previous research projects [34,35].

A total of 80 volunteers and 80 comparison group members will be recruited to the study, reflecting current volunteer numbers.

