Program Coordinators: Each site has an employed program coordinator with tertiary qualifications in social work or a related field. The program coordinators are responsible for recruiting and training the volunteers, establishing referral networks, matching volunteers with families, providing regular supervision to volunteers, conducting intake and progress interviews with families, and referring families to other services within the community.Trained volunteers: All community volunteers participate in a minimum of 30 hours of training before being matched with a family and must participate in two additional capacity-building sessions each year. Examples of core training modules include “a strengths-based approach to working with families,” “reflection on personal values and attitudes,” “boundaries and self-care,” “child development,” and “community resources.” The topics for ongoing capacity-building sessions are decided by the program coordinator depending on family needs at the time. For example, if there are high numbers of families who have infants, topics like “breastfeeding” or “sleeping and settling” may be chosen. All volunteers undergo a background check.Matching: Program coordinators match families with a volunteer, guided by the needs of the family but limited by the pool of volunteers available.Home visits: Volunteers visit the family for approximately 2 hours every week. What happens during visits will depend on the needs of the family. Volunteers are encouraged to support families to connect with other services and facilities within the community (eg, attend local playgroups, visit the child and family health center, go to the park, etc) and link them with information as needed. Volunteers are also expected to model positive interactions with the children and encourage the parents in their personal and family goals. Volunteers do not do cooking or housework tasks unless it is with the parent as part of helping them to learn how to do these tasks, and they do not provide child-minding or child care such as changing nappies or bathing children. Volunteers complete checklists following each home visit, detailing the activities and topics of discussion with the family and whether information was provided to the family or the family linked with another service in the community. The collated data are used as a measure of program fidelity and provide ongoing quality feedback to the service partner organizations.Exit interviews: The duration of the service will be a minimum of 3 months and a maximum of 12 months. When the family, volunteer, and program coordinator agree that the family has met their goals, the family is exited from the program and referred to other services by the program coordinator as appropriate.

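### The volunteer study enrols current volunteers, most of them probably already trained, so it does not identify the effect of taking up volunteering that its research question asks about

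*Protocol article*

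**What the plan says.** The enrolment rule appears in three places in the protocol article. Eligibility Criteria: "All current volunteers within the Volunteer Family Connect program will be invited to participate in the study". Recruitment: "An invitation will be extended to all volunteers currently involved with the 7 participating sites to participate in the research". Sample Size: "A total of 80 volunteers and 80 comparison group members will be recruited to the study, reflecting current volunteer numbers". Study Design adds that the partners deliver the programme "with their current volunteer providers using guidelines to support quality service provision".

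Delivery in the Trial fixes the order of exposure: "All community volunteers participate in a minimum of 30 hours of training before being matched with a family". Table 1 labels the first volunteer survey as enrolment (baseline), with repeats at 6 and 12 months.

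The question to be answered is the fourth under Secondary Research Questions: "Does volunteering on the Volunteer Family Connect program lead to differing outcomes on measures of well-being, health, community connectedness, and self-efficacy", over time and against a matched community group. Eligibility Criteria describes that group: "a community comparison sample will be recruited that will be matched on age, gender, education and employment levels, and geographical location". Quantitative Analysis plans a cross-sectional comparison for the volunteer outcomes.

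The article does not place the volunteer baseline before training or first match. It does not mention length of service as something to be recorded or used.

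**The concern.** The question concerns what taking up volunteering does to a person. That calls for a first measurement before exposure starts. Here the people invited are those already in the programme, and exposure starts with training.

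The article itself gives reason to expect early gains. Its Introduction cites gains in knowledge, skills, confidence and social cohesion among volunteers. One core training module covers community resources, and knowledge of such resources is among the volunteer outcomes in Table 1. Part of the expected benefit may therefore precede the first survey. Some volunteers whom the role did not suit may also have left before it.

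At stake is the conclusion of the volunteer study. A null change could be read as no benefit when the benefit came earlier. A difference in level could be read as benefit when it reflects who volunteers and who stays. Demographic matching addresses neither.

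**Working it through.** The article gives no power or effect figure for the volunteer study, so there is none to reproduce. The check is first one of logic, then of illustrative size.

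**What each comparison estimates.** Write the following, all as volunteers minus comparators:
- S: difference that existed before anyone volunteered (self-selection)
- R: difference created because those who did not suit the role left before enrolment
- A: effect of volunteering accrued before the survey called baseline
- N: effect accrued during the 12 months of follow-up

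The effect of taking up volunteering is A + N.
- A cross-sectional comparison at 12 months estimates S + R + A + N. It equals the target only if S + R = 0.
- A change-from-baseline comparison estimates N, if S and R are stable. It equals the target only if A = 0.

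With current volunteers and no service dates, neither condition can be checked. Replacing the cross-sectional comparison by a change analysis therefore does not cure the problem. With a baseline before training, A = 0 by design and the baseline difference shows S directly.

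**Inputs for the illustrations.** From the article: 80 versus 80, two-sided alpha 0.05, and an effect of about 0.5 SD regarded as meaningful. Everything else below is assumed.

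**Illustration 1, the planned cross-sectional comparison.** Power = Φ(d / √(2/80) − 1.96), with √(2/80) = 0.158.
- d = 0.5: Φ(3.16 − 1.96) = 0.89
- Detectable difference at 80% power: (1.96 + 0.84) × 0.158 = 0.44 SD

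Now suppose there is no causal effect (A + N = 0) but S + R is not zero. Probability of a significant result favouring volunteers:

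| Assumed S + R (SD) | Probability |
|---|---|
| 0 | 0.025 |
| 0.2 | 0.24 |
| 0.3 | 0.48 |
| 0.5 | 0.89 |

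**Illustration 2, a change analysis (not what the article plans).** Assume a total effect of 0.5 SD, the part not yet accrued appearing in full within follow-up, and a correlation ρ between baseline and 12 months of 0.5 to 0.7. The SD of change is √(2(1 − ρ)), which is 1.00 for ρ = 0.5 and 0.77 for ρ = 0.7.

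| Share accrued before baseline | Visible change (SD) | Power, ρ = 0.5 to 0.7 |
|---|---|---|
| 0 | 0.50 | 0.89 to 0.98 |
| 1/2 | 0.25 | 0.35 to 0.53 |
| 3/4 | 0.125 | 0.12 to 0.17 |
| all | 0 | 0.025 in favour of volunteers |

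**Illustration 3, share of the benefit seen as 12-month change.** Assume benefit rises to a plateau with half-life h. For t months already served, share = exp(−kt) × (1 − exp(−12k)), with k = ln 2 / h.

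| Months served, t | h = 6 months | h = 12 months |
|---|---|---|
| 0 | 75% | 50% |
| 6 | 38% | 35% |
| 12 | 19% | 25% |
| 24 | 5% | 13% |

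The curve, the half-lives and the service lengths are all assumptions. Illustrations 2 and 3 apply only to a change analysis.

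**The case against.** There are five fair replies.

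1. *Prior exposure is inferred.* The article gives no length of service. Current volunteers may include people still in training or not yet matched, and the Abstract speaks of at least 80 volunteers, so later entrants are not excluded. This stands. A reader might infer that the whole sample is measured after exposure, but the article supports only that most probably are.

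2. *Follow-up is still informative.* Serving volunteers go on visiting weekly and attend two further capacity-building sessions a year. Three surveys against matched non-volunteers can describe continued volunteering. This stands too. It would be too strong to say that the study can show nothing; what it does not identify is the effect of starting.

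3. *The percentages concern an analysis that is not planned.* Correct. A comparison of levels keeps the accrued benefit, and its weakness is selection and retention. One might infer that it must overstate the effect, but the article gives no drop-out figure and the direction is only likely.

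4. *The detail may lie elsewhere.* The Discussion describes a matched comparison study of volunteering alongside the trial. Baseline timing and service dates could be in its full protocol, and their absence from an article is not in itself a fault. However, the enrolment rule and the causal question are both stated in the article, and they do not fit each other as written.

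5. *Volunteers could not be randomised.* The reason given, that it would halve the pool, is sound. It does not bear on when the baseline is taken, because surveying a recruit before training removes nobody from service.

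**Conclusion.** The point holds in limited form. As enrolled, the volunteer study does not identify the effect of taking up volunteering, which is what the fourth secondary question asks. A change analysis would lose any benefit already accrued, and the planned comparison of levels cannot separate that benefit from self-selection and retention.

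This rests on two things: that most current volunteers had been trained by the first survey, which follows from the enrolment wording and the train-before-match rule but is not stated; and that some benefit comes early, which the article's own account of training and prior evidence makes plausible.

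The size is unknown because length of service is not given. The figures above show only that modest assumed values matter at 80 versus 80.

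A reader might extend this to the main trial. That is not supported: the primary question, the hypothesis and the rule for declaring the programme effective concern families only, and the family comparison is randomised. The volunteer question is secondary and non-randomised.

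**What to change.** 1. Record the dates of training and of first family match for every volunteer, including those already enrolled.
2. Report and analyse volunteer outcomes by length of service at baseline.
3. Give volunteers whose baseline preceded training or first match, with their matched comparators, as a separate analysis. Survey any further new volunteers at induction, before training.
4. Reword the fourth secondary question. Results from volunteers already serving should be described as an association with ongoing volunteering. Causal wording should be kept for those with a pre-exposure baseline, and even there qualified as a non-randomised comparison.

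The cost is two dates per volunteer and a survey at induction; coordinators already recruit and train volunteers. The new-volunteer subgroup will be small, since data collection was underway, was due to end in 2018, and needs 12 months per volunteer. If it came to 20 versus 20 (an assumption), the detectable difference at 80% power would be 0.443 × √(80/20) = 0.89 SD. For that reason the subgroup should supplement the full sample and not replace it. The remaining cost is a more modest conclusion about benefit to volunteers.
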